**Methods:**

A total of 400 individuals from nine PR centers across Canada, Europe, and Australia will be recruited to participate in a randomized controlled trial. Individuals with COPD who have a self-reported decline in balance, a fall in the last 2 years, or recent near fall will be randomly assigned to an intervention or control group. The intervention group will undergo tailored balance training in addition to PR and will receive a personalized home-based balance program. The control group will receive usual PR and a home program that does not include balance training. All participants will receive monthly phone calls to provide support and collect health care utilization and loss of productivity data. Both groups will receive home visits at 3, 6, and 9 months to ensure proper technique and progression of home exercise programs. The primary outcome will be incidence of falls at 12-month follow-up. Falls will be measured using a standardized definition and recorded using monthly self-report fall diary calendars. Participants will be asked to record falls and time spent performing their home exercise program on the fall diary calendars. Completed calendars will be returned to the research centers in prepaid envelopes each month. Secondary measures collected by a blinded assessor at baseline (pre-PR), post-PR, and 12-month follow-up will include clinical measures of balance, balance confidence, functional lower body strength, and health status. The cost-effectiveness of the intervention group compared with the control group will be evaluated using the incremental cost per number of falls averted and the incremental cost per quality-adjusted life years gained.

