### Study Design

We will conduct a multi-center RCT with allocation concealment as well as blinding of the outcome assessors and data analysts to group allocation. A participant flowchart is outlined in Figure 1.

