#### Intervention: Tailored Balance Training

Participants randomized to the intervention group will receive a 30-minute balance training session twice per week in addition to usual PR, and will be asked to complete a third session at home each week, for a total of 90 minutes of balance training per week. This is in keeping with best practice guidelines for older adults and the design of our previous RCT in COPD [32,35,39]. The balance exercises (see Multimedia Appendix 1) will be tailored to emphasize the areas found to be most deficient in COPD [17]. Participants will receive balance training in a separate location or at a separate time from the control group. Sessions will be supervised by physiotherapists using a circuit training approach. While participants may work through stations in groups, each participant will receive individualized exercise prescription based on their baseline balance assessment, as well as recommendations for individualized exercise progression. Our previous trial demonstrated the feasibility of this approach [34]. Participants will also receive an instruction booklet that outlines their individual exercises for the once-weekly, home-based balance training session during PR.

After completion of PR, participants will complete the prescribed home-based balance training program three times per week. The home-based program will follow for the duration of the 12-month follow-up period.

Participants will receive monthly phone calls from their physiotherapist to provide support and problem solve any issues, as well as home visits at 3, 6, and 9 months to ensure proper technique and progression at home.

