### Outcomes

Outcome measures will be collected by a blinded assessor at baseline, at the end of PR, and at 12-month follow-up.

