#### Primary Outcome

The primary outcome measure will be incidence of falls at 12-month follow-up. A fall will be defined as “an incident in which the body unintentionally comes to rest on the ground or other lower level which is not as a result of a violent blow, loss of consciousness, sudden onset of paralysis as in a stroke or an epileptic seizure” [40]. Based on published consensus [41], the participants will be asked, “Have you had any fall including a slip or trip in which you lost your balance and landed on the floor or ground or lower level?” Falls will be measured using monthly fall diary calendars, which are the recommended methodology for falls reporting in clinical trials [41]. All participants will receive the fall diary calendars at the time of the baseline assessment.

Participants will be asked to record falls and time spent performing their home exercise program on the fall diary calendars. They will also be asked to contact the research assistant in the event of a fall or health-related event to ensure all relevant information is included and to return completed diaries in prepaid envelopes to the research center each month. Participants who do not return the calendars or those with unclear data will be telephoned to collect the information.

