### Economic Analysis

An economic analysis will be conducted alongside the trial using the primary outcome (ie, number of falls) and health utilities as effect measures. We will use methods consistent with standard texts and guidelines for economic evaluation [57]. The time horizon of the analysis will be the period of study follow-up (ie, 12 months). Both societal and health care payers’ perspectives will be used for the analysis.

Health care resource utilization and loss of productivity related to falls and COPD will be collected during monthly phone calls to participants. During the monthly phone calls, the participants will be asked if they have had any health care appointments (ie, family doctor, walk-in/urgent care clinic, or specialist), emergency room visits, or hospital stays related to having COPD or a fall. If the participant responds “yes,” the physiotherapist will then ask for details about which health care professionals were seen; what tests, medications, or treatments were ordered; and, if they were hospitalized, for how long.

The time it takes for therapists to administer the rehabilitation exercises, monthly phone calls, and home visits in both intervention and control groups will also be recorded. These resource utilizations will be converted to direct medical costs using country-specific unit costs. Indirect costs may include the productivity loss for patients, if still working, or family members who provide care/assistance to the participating patient.

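### The general claim of blinded outcome assessment does not fit falls, which unblinded participants report, or health-care use, which the supporting physiotherapist elicits

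*Protocol article*

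**What the plan says.** Study Design describes the trial as having "allocation concealment as well as blinding of the outcome assessors and data analysts to group allocation". The Outcomes section, which contains the primary outcome, opens with "Outcome measures will be collected by a blinded assessor at baseline, at the end of PR, and at 12-month follow-up". Neither sentence makes an exception. The abstract is narrower: it speaks of "Secondary measures collected by a blinded assessor at baseline (pre-PR), post-PR, and 12-month follow-up" and describes falls separately, as self-reported.

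Under Primary Outcome, falls come from monthly diary calendars that participants fill in and post back. Participants are also asked to contact the research assistant after a fall. For gaps, "Participants who do not return the calendars or those with unclear data will be telephoned to collect the information"; the caller is not identified.

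The same section defines a fall so as to exclude events caused by a blow, loss of consciousness, stroke paralysis or a seizure. The question put to participants begins "Have you had any fall including a slip or trip in which you lost your balance and landed on the floor" and repeats none of these exclusions.

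Under Economic Analysis, health-care use and lost productivity related to COPD or a fall are collected in the monthly calls. If a participant reports any care, "the physiotherapist will then ask for details about which health care professionals were seen". For the intervention arm, the section on tailored balance training says "Participants will receive monthly phone calls from their physiotherapist to provide support and problem solve any issues".

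**The concern.** In an open-label exercise trial, blinding of the people who collect and classify outcomes is the main safeguard against reporting or probing that depends on allocation. A reader of Study Design and Outcomes would conclude that this safeguard covers the primary outcome and the economic data. The later sections describe collection routes to which it does not apply, or is not said to apply.

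Two results depend on this. The fall count is both the primary outcome and the effect measure for the incremental cost per fall averted. Fall- and COPD-related care feeds the cost side of that ratio and of the cost per QALY. Blinded analysts, which the plan does have, cannot repair a count that differs by arm because of how it was obtained.

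The gap between the definition and the question adds a smaller problem. If no one applies the exclusions, the analysed count is all reported falls; if someone does, it is falls meeting the definition. The article does not say which count is primary, or who decides and with what knowledge of the arm.

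**Working it through.** **Step 1. Who handles each type of data (protocol article).**

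| Data | Recorded by | Followed up by | Blinding stated for that route? |
|---|---|---|---|
| Balance, balance confidence, chair stand | Assessor at three visits | - | Yes (Outcomes; abstract) |
| Falls | Participant, monthly diary | Research assistant; unnamed telephone caller | No |
| Care and productivity loss related to COPD or a fall | Monthly call | Physiotherapist takes the details | No |

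The statement at the head of Outcomes names an assessor and three time points. A monthly diary kept by the participant fits neither. Participants cannot be unaware of balance training, and no participant blinding is claimed. In the intervention arm the monthly caller also supports the home balance programme, so that person knows the arm. The Allocation section adds that site coordinators are told the allocation. The diary holds both falls and home-exercise time, so anyone reviewing it for unclear entries sees exercise information as well.

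**Step 2. Definition against question.** The final part of the participant question can be read in two ways. If loss of balance qualifies every fall, a participant who faints may answer no, which agrees with the definition. If it qualifies only slips and trips, the same participant may answer yes, which does not. Falls caused by a blow are not clearly handled under either reading. The article describes gathering fuller information after a fall, but no masked step that applies the definition to it.

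**Step 3. The plan's own figures (Sample Size Calculation).** Inputs: rates 1.20 and 0.84 per person-year, 80% power, 5% type I error (taken as two-sided), nine centers, coefficient of variation 0.10.

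- Per arm: (1.96 + 0.8416)² × (1.20 + 0.84) / 0.36² = 123.5, so 124. This agrees.
- With clustering, y per arm per center = 2.04 / [8 × 0.36² / (1.96 + 0.8416)² − 0.10² × (1.20² + 0.84²)] = 18.4, so 19, and 9 × 19 = 171. This agrees.

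These figures are not in dispute. They serve only as the base for the illustration.

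**Step 4. Illustration, with an assumed under-count.** Suppose a fraction u of intervention-arm falls is not counted and control-arm counting is complete. The documents give no value for u. The observed rate ratio is the true ratio × (1 − u).

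| u | True 1.00 reads | True 0.70 reads |
|---|---|---|
| 5% | 0.95 | 0.665 (about 0.67) |
| 10% | 0.90 | 0.63 |

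At u = 10% the shift is 10 percentage points when there is no effect, and 7 points (7/30, about 23% of the planned 30% reduction) when the planned effect is true.

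For the chance of a false positive when the true ratio is 1.00, take a = 1.20 and b = 1.20 × (1 − u). The Poisson standard error is √[(a + b)/171]. With the plan's clustering term it is √{[(a + b)/19 + 0.10² × (a² + b²)]/9}.

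- u = 5%: difference 0.06, standard errors 0.117 and 0.129, rejection in 8.1% and 7.5% of trials.
- u = 10%: difference 0.12, standard errors 0.115 and 0.127, rejection in 18.0% and 15.6% of trials.

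The nominal level is 5%. Extra-Poisson variation, which the planned negative binomial model allows for, would widen the standard errors and lower these percentages. It would not alter the shift in the rate ratio.

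**Step 5. Excluded events, also assumed.** If a fraction e of control-arm reported falls are of excluded types, and those falls occur at the same rate in both arms, a true 30% reduction reads 30% × (1 − e): 28.5% at e = 5% and 25.5% at e = 15%. This dilutes the effect, so it acts against the intervention.

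**The case against.** The strongest reply is that the abstract already ties the blinded assessor to the secondary measures and calls falls self-reported. The three visits named under Outcomes plainly describe clinic assessments, so the fault is loose wording. That is largely right about the intended meaning. However, Study Design and Outcomes still say more than the abstract, and Outcomes does so directly above the primary outcome.

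A reader might infer that the physiotherapist elicits the fall count. The documents do not support this. Falls go from the diary to the research center, the research assistant is the contact after a fall, and the physiotherapist's questions under Economic Analysis concern care and productivity. That the unnamed caller for missing calendars is the physiotherapist would be a guess.

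A reader might also infer that falls are never classified blind. The article is silent on this, and the full protocol may contain such a step. What can be said is that none is described, although the definition needs one.

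A reader might further infer a bias in favour of the intervention. Both arms receive monthly physiotherapist calls and home visits at 3, 6 and 9 months, intended to equalise attention. Nothing shows less probing in one arm, and closer contact could raise reporting as easily as lower it.

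Diaries are the recommended method, the question is said to rest on published consensus, and neither choice is challenged here.

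**Conclusion.** The point holds as a mismatch between a stated design property and the data collection described. Blinded assessment, claimed without exception, applies to the assessor-collected clinical measures. It does not extend to falls, which are reported by participants aware of their arm with follow-up of unstated blinding. Nor does it extend to health-care use, which the supporting physiotherapist elicits and who, in the intervention arm, necessarily knows the allocation. The exclusions in the fall definition have no counterpart in the participant question and no described masked step to apply them.

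The documents do not establish that any bias exists, which way it would run, or how large it would be. The 5%-10% under-count and the 5%-15% share of excluded events are assumptions. They show only that modest differences in ascertainment would matter at this sample size. The point calls for corrected wording and a modest procedural safeguard. It does not invalidate the primary outcome or the use of diaries.

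**What to change.** 1. **Wording.** In Study Design and Outcomes, restrict the blinding statement to the assessor-collected clinical measures, in line with the abstract. State that falls and health-care use are reported by unblinded participants.

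2. **Falls.** Have the research assistant already named under Primary Outcome, kept unaware of allocation and using a fixed script, take fall reports and make the calls about missing or unclear calendars. Classify each reported fall against the existing definition from a short circumstances record, with arm and exercise-time entries masked. Take falls meeting the definition as the primary count and all reported falls as a sensitivity analysis.

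3. **Health-care use and productivity.** Where feasible, have the same masked person ask these questions. Otherwise keep the existing caller, with an identical fixed script in both arms.

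**Cost.** Items 1 and 2 need a short form per fall, masking of the exercise entries, and acceptance of a more modest blinding claim. Moving the interview in item 3 would add a second short monthly call for every participant, up to 400 × 12 = 4,800 calls, which is why the common script is offered as the alternative. Participants may reveal their arm during a call, so masking of the research assistant will be imperfect; any known unmasking should be recorded.

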### Data Collection

All subject data will be deidentified and coded with a unique study identifier. Data collection forms and digital files will be securely stored as per the REB protocols.

Each site will be responsible for entering deidentified participant data into a digital database and securely sharing it with the lead investigators and central data analyst for analysis. Only the lead investigators and central data analyst will have access to the final dataset.

A data monitoring committee will be set up to monitor the trial for possible harmful effects. The committee will evaluate any adverse events to recommend whether the study should continue, be modified, or stopped due to safety concerns.

### Data Analysis

The data analysts on the research team will be blinded to group allocation. Descriptive summary statistics will be reported using mean, median, and standard deviation for continuous measures, and frequency and counts for categorical variables. For the primary outcome, we will use random effect Poisson (Negative Binomial) regression model to compare the number of falls at 12-month follow-up between intervention and control groups adjusting for potential confounders, repeated measures, and clustering of participants within centers. For secondary outcomes, we will use random effect linear regression to compare intervention and control groups adjusting for potential confounders and clustering of the observations. For all measures, we will perform intention-to-treat and per protocol analysis.

We will estimate the total cost for the intervention and control groups and calculate the difference between the two groups. Similarly, for the effect measures, we will calculate the difference in the number of falls and in the QALY between groups. The summary measure for the economic analysis will be the incremental cost per number of falls averted (cost-effectiveness analysis) and the incremental cost per QALY gained (cost-utility analysis) for the intervention group compared with the control. Given that this economic analysis will be using data primarily from study participants, nonparametric bootstrap will be used to calculate the 95% confidence interval around the incremental ratios. The decision uncertainty will be presented using cost-effectiveness acceptability curves that show the probability of the intervention being cost-effective compared with the control group at a wide range of willingness to pay for a QALY [57].

No interim or subgroup analysis is planned. We will perform both intention-to-treat and per protocol analyses.

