##### Health Status

Health status is an important patient-reported outcome that describes health-related quality of life of patients. The European Quality of Life 5-Dimension Questionnaire (EQ-5D-5L) will be used to measure health status. It consists of five questions covering dimensions of mobility, self-care, usual activities, pain/discomfort, and anxiety/depression with five response options indicating *no*, *mild*, *moderate*, *severe*, and *extreme* problems for each dimension [53]. The answers to the five questions included in this instrument can be converted to health utility which is an index score anchored at 0 (equivalent to dead) and 1 (for full health), with negative scores for worse than dead. The EQ-5D-5L-derived health utilities will be calculated using the recently developed scoring algorithm for Canada [54] and United Kingdom [55] and the interim algorithm for Australia and Portugal [56]. The EQ-5D-5L will be administered at baseline and at 6- and 12-month follow-up, and then used to determine quality-adjusted life years (QALY) for each respondent. For this study, the resulting adjustment is an adjustment on quality of life as we do not anticipate any differences in survival.

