### Sample Size Calculation

First, we calculated the sample size for an individually randomized two-arm study with 80% power and 5% type I error. We estimated the rate of falls for the control group as 120 per 100-person years, consistent with prospective studies documenting fall rates in similar populations of patients with COPD in Canada and Australia [7,10]; the rate of falls in the intervention group was estimated as 84 per 100-person years, which corresponds to a 30% reduction in the rate of falls. A 30% reduction in fall rate is widely used as a clinically significant threshold in fall prevention studies and is consistent with meta-analyses demonstrating the effect of multi-component exercise on fall rate. Based on this data, the estimated number of participants in each arm with 1-year follow up is 124 patients. However, our study is a multicenter study in which participants are clustered within nine centers. Assuming a coefficient of variation of size 0.10, we need, on average, 19 participants in each arm per site, corresponding to a total of 171 participants in each arm, to account for the clustering of the study [58].

Assuming a similar clustering effect for the secondary outcomes with a sample size of 171 participants in each arm and nine centers, our study has 80% power with 5% type I error to detect differences of the following magnitudes (MCID: minimal clinically important difference):

Berg Balance (SD=6.15, MCID=5) differences of 3.0 units or larger.BESTest (SD=13, MCID=13) differences of 6.4 units or larger.ABC (SD=23.2, MCID=19) differences of 11.5 units or larger.Chair stand (SD=4.8, MCID=3) differences of 2.4 units or larger.

These values are close to half the standard deviation of the outcome measures and are sufficient to detect clinically important changes [45].

We anticipate a loss to follow-up of 15%-20% based on previous trials in PR and have inflated our sample size to 400 participants (200 in each arm) to account for this. Should a participant be unable to attend an assessment session at a study center, we will minimize loss to follow-up by offering to complete assessments in the participants’ homes.

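### A bootstrap 95% CI on the cost-effectiveness ratios themselves misleads if the effect difference straddles zero, and cost per fall averted has no other joint measure of uncertainty

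*Protocol article*

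**What the plan says.** The Data Analysis section of the protocol article names two summary measures for the economic analysis: incremental cost per fall averted and incremental cost per QALY gained. For their uncertainty, "nonparametric bootstrap will be used to calculate the 95% confidence interval around the incremental ratios". It gives no rule for replicates with a zero or negative effect difference, and it mentions neither the cost-effectiveness plane nor net benefit.

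Two other commitments in that section bear on the point. The components are reported separately: besides the cost difference, "we will calculate the difference in the number of falls and in the QALY between groups". Decision uncertainty is shown by acceptability curves, described only "at a wide range of willingness to pay for a QALY".

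The Economic Analysis section sets a 12-month horizon. Health Status says "The EQ-5D-5L will be administered at baseline and at 6- and 12-month follow-up", and that "we do not anticipate any differences in survival", so any QALY gain must come from utility differences within one year. The article states no expected QALY difference, QALY SD, cost difference or cost SD.

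**The concern.** The ratio of cost difference to effect difference has a pole at zero effect, and its sign does not identify the conclusion. A negative ratio can mean cheaper and better (dominant) or dearer and worse (dominated). A positive ratio can mean dearer and better or cheaper and worse. Once replicates cross zero effect, ranking them by the ratio puts opposite conclusions side by side, and the 2.5th and 97.5th ranked values are not limits of anything useful.

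At stake is how the economic result would be read. An interval from a negative to a positive cost per QALY looks like possible savings, when most of the negative replicates may be ones in which the intervention costs more and does worse. For cost per fall averted, no other planned summary treats cost and effect jointly.

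**Working it through.** **1. The plan's own figures.** Inputs from Sample Size Calculation: 1.20 and 0.84 falls per person-year (difference 0.36), an "individually randomized two-arm study with 80% power and 5% type I error", coefficient of variation 0.10, nine centers, 200 enrolled per arm, 15%-20% loss. Two-sided testing is assumed.

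- Before clustering: n = (1.960 + 0.842)^2 x (1.20 + 0.84) / 0.36^2 = 7.849 x 2.04 / 0.1296 = 123.5, so 124 per arm, as stated.
- With clustering: centers needed = 1 + 7.849 x [2.04/y + 0.10^2 x (1.20^2 + 0.84^2)] / 0.1296. At y = 18 per arm per site this is 9.16; at y = 19 it is 8.80, which fits nine centers. 9 x 19 = 171 per arm, as stated.
- 20% loss from 200 leaves 160 per arm. The range 160-171 is used below.

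**2. What goes wrong when replicates straddle zero (all inputs assumed).** Take a QALY gain of 0.01 with SE 0.022 (SD about 0.20 at this sample size), and an extra cost of $500 with SE $300, independent and normal.

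- Point ratio: 500 / 0.01 = $50,000 per QALY.
- Share with non-positive effect: Phi(-0.01/0.022) = Phi(-0.455) = 32%.
- Share with positive extra cost: Phi(500/300) = Phi(1.667) = 95%.
- Dominated: 0.325 x 0.952 = 31%. Dominant: 0.675 x 0.048 = 3%.
- Simulated percentile interval of the ratio: about -$0.33 million to +$0.34 million.

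About 34% of the ratios are negative, and roughly nine in ten of those are dominated rather than cost-saving.

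Net benefit on the same inputs behaves normally. At an illustrative $50,000 per QALY it is 50,000 x 0.01 - 500 = 0, with SE = sqrt((50,000 x 0.022)^2 + 300^2) = 1,140 and 95% limits of about -$2,235 to +$2,235.

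**3. When the ratio interval is harmless.** With an assumed gain of 0.05, SD 0.15 (SE 0.15 x sqrt(2/171) = 0.0162) and the same cost inputs, only about 0.1% of replicates have a non-positive effect. The ratio is $10,000, with limits of about -$2,000 to +$35,000, and about 98% of the negative ratios are dominant. The negative end then means what a reader would take it to mean.

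**4. How often the QALY difference straddles zero.** SE = SD x sqrt(2/n), from 0.10 x sqrt(2/171) = 0.0108 to 0.25 x sqrt(2/160) = 0.0280. The chance that the 95% CI includes zero is 1 - Phi(d/SE - 1.96) - Phi(-d/SE - 1.96), where d is the true gain.

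| True gain (assumed) | SD 0.10, n = 171 | SD 0.25, n = 160 |
|---|---|---|
| 0.01 | 85% | 94% |
| 0.02 | 54% | 89% |
| 0.03 | 21% | 81% |
| 0.05 | 0.4% | 57% |

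**5. Falls.** Power of 80% means that the effect interval includes zero in about 20% of trials when the design effect is real, and in more if the effect is smaller. A direct check at 171 per arm, ignoring clustering:

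- Poisson: SE = sqrt(2.04/171) = 0.109; the interval includes zero in 9% of trials.
- Assumed dispersion 1: SE = sqrt((2.04 + 1.44 + 0.7056)/171) = 0.156; 37% of trials.

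In a trial whose estimate equals 0.36, the share of replicates at or below zero is only 0.05% (Poisson) or 1.1% (dispersion 1).

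**The case against.** The strongest reply has five parts.

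- **The size rests on assumptions.** A reader might infer from the one-year horizon and the absence of an expected survival difference that a QALY interval crossing zero is near-certain. The documents do not support that. They state no QALY effect or SD, and the chance runs from under 1% to 94% over the assumed ranges. The intervention also targets balance, balance confidence and leg strength, which could move mobility and usual-activity scores without passing through falls. This stands, and it limits the claim.
- **Much is already covered.** Separate cost and effect differences are planned, and the QALY acceptability curve remains valid with zero or negative effects. This stands for QALYs. For falls, the primary regression and the separate difference show whether the effect may be zero, but neither describes cost and effect together.
- **The interval type is left open.** The article does not specify a percentile interval, commits to standard texts, and may leave construction to an analysis plan. This helps only in part. The sentence fixes the ratio as the target, and percentile-type bootstrap intervals all rank the replicate ratios. A method that orders replicates on the plane would escape the problem, but the text does not call for one.
- **Falls replicates rarely cross zero at the design effect.** This is correct when the estimate reaches 0.36. It gives no protection when the estimate falls short.
- **It is a secondary analysis, and the replicates can be summarised again later.** This stands and bears on severity.

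**Conclusion.** The concern holds in a limited form. The article states a rule that gives misleading limits whenever effect replicates straddle zero, and nothing in the text handles that case. It is plausible to likely for cost per QALY if the true gain is about 0.01-0.02 (54%-94% of trials), uncertain at 0.03 (21%-81%), and anything from negligible to about even at 0.05 (0.4%-57%). These figures rest on assumed SDs of 0.10-0.25, 160-171 per arm and a normal approximation.

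For cost per fall averted the risk is about 20% at the stated power if the design effect is real, and higher if it is smaller. This is the less protected measure, because the ratio interval is its only joint summary of uncertainty. The point is minor to moderate. It concerns a secondary economic analysis and does not affect the primary falls analysis, the sample size or data collection.

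**What to change.** In Data Analysis:

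- Report each ratio as a point estimate, with the bootstrap replicates on the cost-effectiveness plane and bootstrap CIs for incremental cost and incremental effect.
- Replace the CI of the ratio with a bootstrap 95% CI of incremental net benefit (willingness to pay x effect difference - cost difference). Use a prespecified numeric willingness-to-pay range for QALYs and a separate, sponsor-set range per fall averted.
- Add an acceptability curve for cost per fall averted.

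The cost is a rewording. The same replicates serve, and no new data are needed. There are two drawbacks: readers who expect an interval around the ratio will get a net-benefit interval instead, and the sponsor must choose a willingness-to-pay range per fall, which the article does not give.
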